### Cost measures

Parallel to the RTP study's effectiveness-related aims is a set of aims related to CE. The primary focus of the economic analyses is to compare the operating and reinforcement costs between the IAU and the P4P groups. Operating costs are defined as costs associated with treatment delivery, and reinforcement costs are defined as costs associated with reinforcing superior delivery/implementation of treatment. Additionally, in order to be able to better interpret the findings, it also was necessary to collect information on training costs.

The Treatment Cost Assessment Tool (TCAT) was used to determine operating costs of delivering A-CRA and ACC at each participating AAFT site. The TCAT was developed by Brandeis University in collaboration with Texas Christian University [82] and is an extension of the methods used in the Cost Study of the Alcohol and Drug Services Study (ADSS) [83,84]. The study's TCAT version is a Microsoft^® ^Excel-based workbook that is used to collect information related to a site's clinical activity (*e.g.*, number of clients served, average direct time per treatment session), personnel costs (*e.g.*, percentage of time spent on clinical activities, salary), and non-personnel costs (*e.g.*, supplies, transportation). In contrast to the operating costs, the reinforcement costs are the costs associated with providing the monetary incentives to therapists as part of the RTP study, and are calculated as a total of the payments themselves times (1 + overhead rate of Chestnut Health Systems). The overhead cost is included to reflect the resource costs in administering incentives (*e.g.*, verifying incentive criterion and documenting payments). In the course of completing the TCAT, we will gather data about the persons, steps, and time involved in administering incentives, so we can refine the estimate of administrative costs. Because the clinical training for the AAFT initiative is being funded through a separate CSAT contract, the training costs are those costs incurred by the training contractor in delivering the AAFT training and technical assistance (*e.g.*, trainers, logistics, travel expenses of trainees). A cost per therapist trained will be computed by taking the total cost of the training effort divided by the number of AAFT therapists trained.

### Analytic plan

#### Effectiveness-related analyses

Because of the multilevel nature of the data, Hierarchical Linear Modeling (HLM) [85], which is able to handle this type of data by allowing the relationship between the variables of interest to vary by higher-level groupings (*i.e.*, therapists and/or sites), will be used to analyze the effectiveness-related hypotheses. For H1.1 (*i.e.*, Target A-CRA is more likely for adolescents in the P4P group), the main independent variable is group assignment (IAU versus P4P), and the dependent variable is whether adolescents received Target A-CRA. Adolescents are at level one, therapists are at level two, and sites are at level three. For Hypothesis H1.2 (*i.e.*, Monthly A-CRA Competence is more likely for therapists in the P4P group), the main independent variable is group assignment (IAU versus P4P), and the dependent variable is the percentage of months therapists demonstrated A-CRA competence. Here, therapists are at the lowest level (*i.e.*, level one), and sites are at the next highest level (*i.e.*, level two). For Hypothesis H1.3 (*i.e.*, being in recovery after intake is more likely for adolescents in the P4P group), the main independent variable is group assignment (IAU versus P4P), and the dependent variable is whether adolescents are in recovery post-intake. Again, adolescents are at level one, therapists are at level two, and sites are at level three.

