### Randomization

Although random assignment of therapists might appear ideal, a number of issues made such an approach impractical and led to the decision to randomize in clusters by site. For example, dividing small (two- to four-person) clinical teams within a site through random assignment may lead to unintended consequences due to some therapists being eligible for incentives and others not. For example, the IAU group might work harder than they normally would to achieve goals (*i.e.*, compensatory rivalry), which would threaten the study's internal validity (increasing type 2 error probability). Another possibility is that this situation would lead to resentful demoralization of therapists in the control group, and they would deliver sub-par effort (increasing type 1 error probability). In order to avoid these potential problems, we used an adaptive randomization procedure referred to as urn randomization [71,72] to assign sites to the two study conditions. Shadish, Cook, and Campbell [71] recommend using such adaptive procedures whenever feasible and when good matching variables can be found, and have noted that the best matching variables are pre-test scores on the outcomes of interest.

Given the two cohorts of AAFT grantees were in months 27 and 15 of their respective 36-month grants, pre-test data was available on several important matching variables. Using existing project data on therapists performance and from staff questionnaires (described further below), we created several grantee-level measures including: average Target A-CRA rate; average DSR upload rate; three-month client recovery rate; percentage of Caucasian clients; percentage of Hispanic clients; percentage of male clients; number of therapists; average therapist age; percentage of Caucasian therapists; percentage of male therapists; and AAFT staff ratings of expected performance. This last measure was used to take into account any recent changes (*e.g.*, turnover of supervisor, major improvement/decrements in performance) that might impact performance in the study, and was based upon independent rankings from the director and coordinator of the AAFT training team. Both raters agreed on the rankings for all but two study sites (Kappa = 0.86), and the two raters were able to discuss and resolve these two inconsistencies. Each of the above-mentioned existing measures was then entered by AAFT cohort into an urn randomization software program called gRand.

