**Education**			
Less than Bachelor's Degree	0.0%	7.5%	3.7%
Bachelor's Degree	47.6%	35.0%	41.5%
Master's Degree	50.0%	55.0%	52.4%
Doctoral Degree	2.4%	2.5%	2.4%
			
**Years of SAT Experience**	3.3 (3.3)	5.4 (7.1)	4.3 (5.6)
			
**Self-reported being in recovery**	7.1%	7.5%	7.0%
			
**Pre-RTP Target A-CRA Rate**	21.4%	16.7%	19.2%
			
**Pre-RTP Session Recording Rate**	40.4%	41.7%	41.0%
			
**Pre-RTP 3-month Client Recovery Rate**	46.5%	45.1%	45.9%

Note: No statistically significant differences between conditions

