### Adolescent intake and follow-up measures

In addition to examining the extent to which monetary incentives improve treatment implementation (*i.e.*, delivery of Target A-CRA, demonstration of Monthly A-CRA Competency), a third aim of the RTP study is to examine the extent to which these two implementation measures impacted treatment outcome for the adolescent clients. Being 'in recovery' (*i.e.*, no past month alcohol or other drug use, abuse, or dependence symptoms while living in the community) was selected as the primary outcome of interest, as is consistent with the primary clinical outcome used in the Cannabis Youth Treatment (CYT) study [8]. Intake and follow-up versions of this measure were collected using the GAIN [79], which is a comprehensive biopsychosocial assessment designed to integrate research and clinical assessment into one structured interview. The GAIN's main scales have been shown to demonstrate good internal consistency (alpha greater than 0.90 on main scales, 0.70 on subscales), test-retest reliability (Rho greater than 0.70 on days/problem counts, kappa greater than 0.60 on categorical measures), and to be highly correlated with measures of use based on timeline follow-back methods, urine tests, collateral reports, treatment records, and blind psychiatric diagnoses (rho of 0.70 or more, kappa of 0.60 or more) [79-81]. GAIN data were collected as part of the AAFT project's evaluation and were de-identified prior to being used as part of the RTP study. In order to access this data, the study group sought and received a signed data sharing agreement from each site that explicitly allowed the use of the de-identified adolescent data for the purposes of research, public health, or healthcare operations.

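### The models for H1.1 to H1.3 name only group assignment and leave out the cohort, the pre-test rates that balanced the sites, and recovery status at intake

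*Protocol article*

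**What the plan says.** The section on effectiveness-related analyses gives each hypothesis a predictor, an outcome and a set of nesting levels. For H1.1, "the main independent variable is group assignment (IAU versus P4P), and the dependent variable is whether adolescents received Target A-CRA". For H1.2, again with group as predictor, "the dependent variable is the percentage of months therapists demonstrated A-CRA competence". For H1.3, likewise, "the dependent variable is whether adolescents are in recovery post-intake". No cohort term, allocation variable, pre-test rate or intake value appears in any of the three.

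The Randomization section lists eleven grantee-level measures, beginning "average Target A-CRA rate; average DSR upload rate; three-month client recovery rate; percentage of Caucasian clients; percentage of Hispanic clients", and continues: "Each of the above-mentioned existing measures was then entered by AAFT cohort into an urn randomization software program". It also cites with approval the view that "the best matching variables are pre-test scores on the outcomes of interest".

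On the adolescent recovery outcome, the measures section states: "Intake and follow-up versions of this measure were collected using the GAIN".

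Table 1, which describes therapists (42 P4P, 40 IAU), gives the "Pre-RTP Target A-CRA Rate" as 21.4% in P4P and 16.7% in IAU. The pre-test recovery rate is 46.5% vs 45.1% and the pre-test recording rate 40.4% vs 41.7%. A footnote reports no significant differences between arms.

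**The concern.** The design treats pre-test performance as prognostic when it allocates sites, and the stated models then make no use of it. Two consequences follow.

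The first is precision. When allocation is balanced on variables that predict outcome, the true sampling variation of the arm contrast shrinks. A model that omits those variables still counts their variation as between-site noise, so its standard error is too large, its type I error falls below nominal and power is lost. With 29 randomised units this matters, and the article itself lists limited power among its weaknesses.

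The second is the particular allocation obtained. Table 1 shows P4P ahead by 4.7 points on the pre-test version of the H1.1 outcome. A model without that pre-test value cannot separate such a chance difference from an effect of the incentives. The same contrast is the denominator of the cost-effectiveness ratio.

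**Working it through.** **Check of the plan's own figures.** The article states no sample size, power or alpha to reproduce. The overall rates in Table 1 can be checked as (42 × P4P + 40 × IAU)/82:
- Target A-CRA: (42 × 21.4 + 40 × 16.7)/82 = 19.11. The stated value is 19.2, which is reachable within rounding of the arm rates (up to 19.16).
- Recovery: 45.82 against 45.9 stated, also within rounding (up to 45.87).
- Recording: 41.03 against 41.0 stated.

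**Pre-test differences, P4P minus IAU.** Target A-CRA 21.4 − 16.7 = +4.7 points (ratio 1.28); recovery +1.4; recording −1.3.

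**Model-based variance for H1.1, with and without the site pre-test rate.** From the article: 29 sites. Assumed, because the article gives none of them: a 15/14 split, m = 30 adolescents per site, a rate of p = 0.20 (close to the pre-test 19.2%), ICC 0.10, site-level pre-post correlation r of 0.5 to 0.7, two-sided alpha 0.05 and 80% power. The therapist level is left out for simplicity.

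Var = [ICC·p(1−p)·(1−r²) + (1−ICC)·p(1−p)/m] × (1/15 + 1/14), with p(1−p) = 0.16 and 1/15 + 1/14 = 0.1381. The detectable difference is (2.052 + 0.855) × SE, using t quantiles on 27 df.

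| Model | Site term | Within-site term | Sum | SE | Detectable difference |
|---|---|---|---|---|---|
| No covariate | 0.0160 | 0.0048 | 0.0208 | 5.36 points | 15.6 points |
| r = 0.5 | 0.0120 | 0.0048 | 0.0168 | 4.82 points | 14.0 points |
| r = 0.7 | 0.0082 | 0.0048 | 0.0130 | 4.23 points | 12.3 points |

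The variance falls by 0.0040/0.0208 = 19% at r = 0.5 and by 0.0078/0.0208 = 38% at r = 0.7. Spending one or two degrees of freedom on site-level covariates leaves 14.0 and 12.3 unchanged to one decimal. Across ICC 0.05 to 0.20 and 15 to 50 adolescents per site, the reduction runs from 11% to 45%. The between-site term is 77% of the total in the base case (0.0160/0.0208), but only 44% at ICC 0.05 with 15 per site (0.0080/0.0181).

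**Direction of the error.** A site-level simulation (29 sites, 20,000 replicates, nominal 0.05) paired sites on one prognostic score as a stand-in for the urn. R² is the assumed share of between-site outcome variance that the score explains; power is at an assumed effect of 0.9 site-level SD.

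| R² | Type I error, unadjusted | Type I error, adjusted | Power, unadjusted | Power, adjusted |
|---|---|---|---|---|
| 0 | 0.052 | 0.052 | 0.65 | 0.65 |
| 0.2 | 0.033 | 0.051 | 0.66 | 0.74 |
| 0.4 | 0.019 | 0.050 | 0.67 | 0.85 |
| 0.6 | 0.005 | 0.046 | 0.68 | 0.96 |

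Pairing on a single score balances more tightly than an urn fed with eleven measures, so these losses lie toward the upper end.

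**Intake recovery in H1.3.** The article does not report how many adolescents are in recovery at intake, or how strongly intake status predicts follow-up status, so no gain is computed for that covariate.

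**The case against.** The strongest reply is that this is an article that condenses a fuller plan. Calling group the main predictor leaves room for others, and a covariate list is the kind of detail often left to that plan. This stands in part: the text supports the statement that no covariate is named, not that the analysis will be unadjusted. What remains is that the article sets out predictor, outcome and levels for three models and passes over variables that its own Randomization section treats as important. With eleven candidates and no named set, the choice could be made after the data are seen.

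A reader might infer from Table 1 that a definite part of any H1.1 effect, say 2.4 to 3.8 points at pre-post slopes of 0.5 to 0.8, is inherited from baseline. The documents do not support this. The 4.7 points are a difference between therapists, whereas the urn used grantee averages that are not reported by arm. The pre-test rate is therapist self-report, whereas achievement in the trial needs verification by a rater. The slope would be invented, and the difference is reported as not significant. Nor does omitting a covariate after randomisation bias the contrast on average; the simulation shows a conservative test. The difference is a reason to adjust, not evidence that randomisation failed.

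A reader might also infer that admissions differ by arm, since adolescents enter after sites learn their arm and each Target A-CRA success pays $200. Nothing in the article shows this. If it did occur, it would be a recruitment problem that intake covariates would not fully repair.

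Finally, the recording upload rate is not a pre-test value of the H1.2 outcome. It bears on eligibility to be rated, and no pre-test competence rate is reported. That objection stands in full.

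**Conclusion.** The point holds as a matter of efficiency and prespecification. The models as stated leave out cohort, pre-test and intake values that are already collected, most of which were used to allocate the sites. The likely cost is a conservative test and lost power: an illustrative 19 to 38% of the model-based variance for H1.1, or 1.6 to 3.3 points of detectable difference. This rests on assumed ICC, cluster size, event rate, pre-post correlation and arm split, none of which the article gives. If the pre-test rates do not predict outcome, the gain disappears. The H1.1 estimate is also left exposed to a chance pre-test difference in favour of P4P, of unknown effect. The article does not show that the analysis will be unadjusted or that its result will be biased.

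**What to change.** In the effectiveness-related analyses, name the covariates:
- **All three models:** AAFT cohort.
- **H1.1:** also the site's pre-test Target A-CRA rate.
- **H1.3:** also the site's pre-test three-month recovery rate and the adolescent's own recovery status at intake.
- **H1.2:** the site's pre-test upload rate may be added, described as a proxy.

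Stop there. With 29 sites the eleven allocation measures cannot sensibly enter one model, and this set uses at most two site-level degrees of freedom per model. Report the models with group alone as sensitivity analyses. If a logit link is used, compare the two sets as risk differences, because adjusted and unadjusted odds ratios are not the same quantity.

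The cost is a sentence or two in the plan. No new data are needed.

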#### Cost effectiveness-related analyses

As is the usual case in CE analyses, we hypothesize that the experimental P4P group will be more expensive, but more effective relative to the IAU group. In order to test this general hypothesis, we relate the cost of reinforcement to its impact on each of the study's effectiveness-related hypotheses described in the previous section. In addition to noting whether the P4P group was statistically superior to the IAU group on each outcome, we will report the cost per adolescent receiving Target A-CRA, cost per month of demonstrated A-CRA competence, and cost per adolescent in recovery after intake. Using the notation of Glick and colleagues [86], the CE measure for the RTP study is the ratio of cost (*i.e.*, the difference between the average cost per individual in P4P and the average cost per individual in IAU, denoted by C) divided by effectiveness (*i.e.*, the comparable difference on effectiveness, denoted by Q). That is, CE = C/Q. Our basic CE measure is the CE of reinforcement using each of the measures in this study (*i.e.*, cost per adolescent who receives Target A-CRA; cost per month of demonstrated A-CRA competence; and cost per adolescent in recovery after intake). Each of these measures will be calculated as CE (P4P) = C (P4P)/Q(P4P). Here, C (reinforcement) is the difference in costs between the P4P and IAU groups, converted to the appropriate scale, and Q(P4P) is the corresponding difference in outcomes. Within CE measures, the numerator of each measure is the net cost (difference in cost per client and the grand mean), and the denominator is the net effectiveness (difference in the outcome per client and the grand mean) for each of the three respective outcomes (% of months of A-CRA/ACC competence; % of adolescents receiving Effective Threshold of A-CRA/ACC, and % of adolescents in recovery after intake).

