### 2. Paying the right amount

In order for an incentive to be effective, it must be commensurate with the costs in time and effort associated with achieving the targeted behavior. This is similar to the concept of financial salience being measured as part of the RTP study. Importantly, given the paucity of studies within the field of alcohol and drug treatment that have used P4P methods, determining appropriate incentive amounts was perhaps the most difficult aspect of designing the study. That is, incentive amounts selected had to simultaneously be large enough to significantly improve therapist performance, and small enough to be considered within a practical range for community-based treatment providers to implement.

Calculations suggested that full-time therapists in the P4P condition would earn on average an amount between $1,404 and $2,412 per 12-month period, which equated to approximately 4% to 7% of an average annual therapist salary of $35,000. While we believe these amounts are within a range that is practical for community-based treatment providers, the study will help us learn whether or not these incentives are large enough to impact performance.

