### Study strengths and weaknesses

In addition to the use of random assignment, the RTP study has several other strengths. For example, a unique strength of the RTP study is the level of standardization in regard to the funding and training provided to the 29 participating agencies and their therapists. Specifically, because CSAT's approximately $30 million dollar AAFT initiative provided each of its grantees with close to $300,000 per year (for three years) as well as a comprehensive training and technical assistance package (via a separate training contract), the AAFT initiative provided an ideal opportunity to focus on examining the effectiveness and CE of P4P to improve EBT implementation and subsequent treatment outcomes for clients. Other strengths of the study include its: use of a theoretically-based conceptual framework; multi-site design; relatively large sample size; independent verification of therapist achievement of targeted behaviors; longitudinal assessment of therapist attitudes and client outcomes; inclusion of CE analyses; and hypothesis-driven multilevel analytic plan. Like all studies, however, the RTP study also has some limitations that must be acknowledged. First, although larger than any other known P4P experiment conducted to date, a greater number of sites and therapists would provide more statistical power and better generalizability. A second limitation of the study is that randomization was conducted by grantee rather than by therapist. However, as discussed previously, we believe the potential disadvantages associated with randomizing therapists within site (*e.g.*, compensatory rivalry, resentful demoralization) outweighed its advantages. Finally, because the targets being reinforced as part of this study are specific to the delivery of A-CRA procedures, the findings from this study may not generalize to other interventions and/or healthcare or behavioral health settings.

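### The numerator of all three cost ratios is a plain arm difference that appears to add a small incentive cost to a site-level operating-cost difference across 29 sites; it may be too imprecise to fix even its sign, so its parts should be defined and reported separately

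*Protocol article*

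**What the plan says.** The Cost effectiveness-related analyses section defines the numerator as "the difference between the average cost per individual in P4P and the average cost per individual in IAU, denoted by C", and it serves three ratios: "cost per adolescent who receives Target A-CRA; cost per month of demonstrated A-CRA competence; and cost per adolescent in recovery after intake".

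On what enters C, the Cost measures section states: "The primary focus of the economic analyses is to compare the operating and reinforcement costs between the IAU and the P4P groups". Operating cost is measured at site level: the costing workbook (TCAT) "was used to determine operating costs of delivering A-CRA and ACC at each participating AAFT site". Reinforcement cost is the payments made, scaled up by an overhead rate whose value is not given.

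The analysis section words the numerator in other ways too. It proposes to relate what reinforcement cost to its impact, and it writes "C (reinforcement) is the difference in costs between the P4P and IAU groups, converted to the appropriate scale". Later it says "the numerator of each measure is the net cost (difference in cost per client and the grand mean", which is a deviation from an overall mean and not a contrast of two arms.

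Two figures set the scale. Under Paying the right amount, full-time P4P therapists "would earn on average an amount between $1,404 and $2,412 per 12-month period". Under Study strengths and weaknesses, the initiative "provided each of its grantees with close to $300,000 per year (for three years".

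**The concern.** If C is total cost, it adds two quantities of very different quality. Payments to therapists are known from the study's own records. The operating-cost difference is a contrast of about 14 sites with about 15, each with its own salaries, prices and caseload. The variables listed under Randomization cover performance, clients, staff and expected performance, but not cost. The effectiveness outcomes get multilevel models; for C the article describes only a difference of averages.

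The incentive is small beside a site's budget. A chance imbalance in how expensive the sites are could therefore be as large as the incentive or larger. The reported cost per adolescent reaching Target A-CRA, per competent month and per adolescent in recovery could then come out at several times the incentive cost, or as an apparent saving. Cost-effectiveness is one of the study's primary aims, and the article itself expects P4P to be the more expensive arm.

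**Working it through.** **Inputs from the Protocol article.** 29 sites (Site recruitment); 82 therapists, of whom 42 P4P and 40 IAU (Randomization, Table 1); expected incentive $1,404 to $2,412 per full-time therapist per year and average salary $35,000 (Paying the right amount); about $300,000 per grantee per year (Study strengths and weaknesses).

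**Assumptions.** A 14/15 split of sites; sites weighted equally; P4P leaves operating cost unchanged, so that the true C equals the incentive; overhead zero unless stated; between-site CV of operating cost not given, so a range is shown.

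**1. The article's own figure.** 1,404/35,000 = 4.0% and 2,412/35,000 = 6.9%. This reproduces its 4% to 7% of salary.

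**2. Incentive as a share of a site-year.**
- All therapists: 82/29 = 2.83 per site. 2.83 × $1,404 = $3,970 and 2.83 × $2,412 = $6,820, or 1.32% and 2.27% of $300,000.
- P4P therapists only: 42/15 = 2.8 to 42/14 = 3.0 per site, giving $3,931 to $7,236, or 1.31% to 2.41%.
- With 50% overhead (assumed), the upper figure on the first basis becomes 3.41%.

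Dividing both incentive and operating cost by the same number of clients leaves these shares unchanged.

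**3. Standard error of the operating-cost difference.** As a share of mean site cost, SE = CV × √(1/14 + 1/15) = 0.372 × CV.
- CV 5%: 1.9%
- CV 10%: 3.7% (about $11,100 on $300,000)
- CV 20%: 7.4% (about $22,300)

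The SE equals the whole incentive at a CV of 1.32/0.372 = 3.6% to 2.27/0.372 = 6.1%.

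**4. Chance that C is negative.** This is Φ(−incentive share / SE). For example, at CV 10% and share 1.32%, Φ(−1.32/3.72) = 0.36.

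| CV (assumed) | Share 1.32% | Share 2.27% | Salary only, 4.0% | Salary only, 6.9% |
|---|---|---|---|---|
| 2% | 4% | <1% | <1% | <1% |
| 5% | 24% | 11% | 2% | <1% |
| 10% | 36% | 27% | 14% | 3% |
| 20% | 43% | 38% | 30% | 18% |

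The salary-only columns treat salary as the whole operating cost, the benchmark kindest to the plan. With the 3.41% share (50% overhead), the chance is 18% at CV 10% and 32% at CV 20%.

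**The case against.** The strongest reply is that C may not contain operating cost at all. The analysis section speaks of the cost of reinforcement and attaches that label to C. On that reading C is payments plus overhead, and there is neither operating-cost noise nor any risk to the sign. This stands as a possible reading. The explicit definition and the stated focus on operating and reinforcement costs point to total cost, but the article does not settle it.

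Second, a condensed article need not set out adjustment, price standardisation or intervals, so their absence shows nothing about a fuller plan. That stands, and no such omission is counted here. What is at issue is the definition the article does print. An interval would display the imprecision without reducing it.

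Third, the CV is not in the documents, and the full grant overstates the cost of delivering A-CRA and ACC, because it also pays for GAIN assessment. Both points stand, hence the range and the salary-only columns. Standardised funding may also narrow differences in total spending, although cost per individual would still vary with caseload.

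Fourth, the SE formula ignores the urn randomisation, which was run by AAFT cohort and included number of therapists. To the extent that these predict cost, the SE above is too large. If they predict it poorly, adjusting for them gains little.

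Fifth, P4P rewards a set amount of delivery and may truly change operating cost. Counting operating cost is therefore legitimate, and the true C need not equal the incentive.

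A reader might go further and infer that the sampling error certainly exceeds the incentive, or that the ratios mainly show which sites were expensive. The documents do not support this. It needs a CV above roughly 4% to 6% on the full-grant basis, and no figure places it there. Nor do they show that each site gives a single cost observation: Next steps says the TCAT is still being administered. Repeat rounds would not, however, remove differences between sites.

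**Conclusion.** The point holds as one of definition and precision. The wordings of the numerator do not agree and must be reconciled. If C is total cost, as the definition and the Cost measures section indicate, the incentive is about 1.3% to 2.4% of a site-year before overhead (4% to 7% of salary cost alone), and the SE of the operating-cost difference reaches that size at a CV of roughly 4% to 6%. At a CV of 10% to 20%, with no effect of P4P on operating cost, C would be negative about 27% to 43% of the time, or 3% to 30% on the salary-only benchmark. At a CV of 2% the problem is almost gone. These figures rest on the assumed CV, the 14/15 split and the proxy for operating cost. The difference between randomised arms remains unbiased.

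**What to change.** In Cost effectiveness-related analyses, replace the competing wordings with one definition of C, stated as two separately reported components:

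1. Reinforcement cost: payments plus administration, with its own ratio for each outcome.
2. The operating-cost difference: estimated in a site-level model adjusted for AAFT cohort and number of therapists, both already used in the urn randomisation, with an interval that treats sites as the unit.

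Give the total-cost ratio as the sum of the two, with its uncertainty. Valuing TCAT quantities at common unit prices can be an optional sensitivity analysis. It should not be the base case, because it drops local prices, changes what is estimated and leaves variation in client volume.

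The cost is a change of wording, a little more analysis and additional ratios for each outcome, using data the study already plans to collect. The gain is limited: operating-cost noise is isolated and perhaps reduced, but not removed, and the size of any reduction cannot be computed from the article. The well-measured component would at least be visible on its own.
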